#### Data management {19}

Data will be collected from the online Hospital Management Information System (HMIS) and hospital record files from all clinical trial sites. All relevant data from hospital files will be manually entered in record sheets and CRFs by designated project personnel. The data from record sheets and HMIS will then be transferred to MS Excel sheets. The data files will be accessible to the appointed statistician for data analysis and interpretation.

#### Confidentiality {27}

The hospital record files and HMIS software will be accessible to designated members of the clinical trial team only. All data files will be secured at the office of Clinical Trial Unit (CTU), Dow University of Health Sciences.

#### Plans for collection, laboratory evaluation and storage of biological specimens for genetic or molecular analysis in this trial/future use {33}

Biological specimens of hospitalized patients will be collected and sent to the laboratory by on-duty staff according to the given schedule and as recommended by the treating physician. Discharged patients will be contacted via phone call and their samples will be collected by the study investigators. All samples will ultimately be sent to the laboratory or at predetermined storage conditions.

### Statistical methods

#### Statistical methods for primary and secondary outcomes {20a}

Patients will be randomized at a ratio of 2:1 to receive either C-IVIG with standard of care or standard of care only. The data to be analyzed will be blinded using the SPSS software 24.0. All randomized study participants will be included in the intention-to-treat population and all participants completing the study period will be analyzed (complete case analysis). Normality of continuous data will be checked by the Shapiro-Wilk test, and parametric or non-parametric tests will be applied accordingly. Continuous variables will be presented as mean (± SD) or median (interquartile range), and categorical variables will be presented as percentages. In the primary analysis strategy, we will use the Kaplan–Meier curve (Breslow test) that compares the time to reach the primary end point in the trial groups. Hypothesis testing of outcomes for the assessment of safety and efficacy parameters will be conducted by Mann-Whitney *U* test or independent *t*-test. Categorical data will be compared with chi-square test, and value of the two-sided Fisher exact test will be recorded. An estimate of the relative risk and 95% confidence interval will also be reported. Hypothesis testing will be conducted at a significance level of 0.05.

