#### Criteria for discontinuing or modifying allocated interventions {11b}

Modification of the allocated intervention will be based on the planned interim analysis. Outcome of the interim analysis will lead to making decision regarding selection of higher C-IVIG dose in case of currently selected 0.15 g/kg dose not found efficacious. The higher dose of C-IVIG will be selected from the dosage investigated in previous phase I/II clinical trial [11]. The C-IVIG infusion will be discontinued if any serious adverse event occurs or discontinued on patient request and the patient will be excluded from the study.

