#### Outcomes {12}

Primary outcome:28-day mortality [time frame: 28 days]All-cause mortality of participants will be monitored for 28 days to assess the safety and efficacy of C-IVIG

Secondary outcomes:Immediate (within 24 h) or serious adverse events (throughout the hospital stay) [time frame: 28 days]Clinical status according to 7 category ordinal Scale [time frame: 28 days (till hospital stay)Not hospitalized and no limitations of activitiesNot hospitalized, with limitation of activities, home oxygen requirement, or bothHospitalized, not requiring supplemental oxygenHospitalized, requiring any supplemental oxygenHospitalized, requiring noninvasive ventilation or use of high-flow oxygen devicesHospitalized, receiving invasive mechanical ventilationDeathChange in Horowitz index (PaO_2_/FiO_2_ ratio use to assess lung function) during hospital stay [time frame: 28 days]Change in C-reactive protein (CRP) levels, radiological findings, IL-6 level, and anti-SARS-CoV-2 antibody levels [time frame: 5 days]

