#### Sample size {14}

Three hundred nine participants will be enrolled in the study. Sample size was determined by taking proportion of survival in intervention group (P1) = 75%, proportion of survival in control group (P2) = 40%, power of test (1-β) = 90%, with the sample ratio 2:1 (test to control), superiority margin 0.15, and drop rate 30%. The calculated total sample size is 309 patients, 206 tests and 103 control. The calculated sample size was determined with the help of online sample size calculator (www.riskcalc.org) taking 99% confidence level (11).

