#### Plans to promote participant retention and complete follow-up {18b}

Designated personnel from the trial staff will be appointed to ensure the participant retention and complete follow-up during the participant’s hospital stay and after discharge as well. After a participant’s hospital discharge, participants will be followed on call. The participant can withdraw from the trial at any point. The decision will be communicated with the study investigator; the clinical research associate should be explaining the importance of staying in the trial for the full duration of follow-up. For withdrawal, there is a form in CRF that will be filled by the clinical research associate with reasoning why the participant is withdrawing from the trial. If the participant will be lost to follow-up, the data that will be collected till the time of loss to follow-up will be assessed and used in the analysis.

If the patient will withdraw due to AEs, the clinical associate or the treating physicians will closely monitor the follow-up of AEs until the participants return to the baseline state or the participant condition returns to normal. Then the AEs will be reported to the study investigators.

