#### Methods in analysis to handle protocol non-adherence and any statistical methods to handle missing data {20c}

To handle the missing data multiple imputation will be used or complete case analysis will be used. The primary analysis will use the intention-to-treat principle.

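### The protocol gives unreconciled rules for who is counted in the primary 28-day mortality analysis, and two of them break intention-to-treat

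*Protocol article*

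**What the plan says.** The sole primary outcome is death from any cause by day 28 (Outcomes {12}: "All-cause mortality of participants will be monitored for 28 days to assess the safety and efficacy of C-IVIG"). Five statements in the protocol article bear on who is counted in its analysis.

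- **Statistical methods {20a}:** "All randomized study participants will be included in the intention-to-treat population".
- **Same sentence of {20a}:** "all participants completing the study period will be analyzed (complete case analysis". The section then names a Kaplan–Meier comparison with the Breslow test as the primary analysis strategy, and adds a relative risk with a 95% confidence interval.
- **Missing data and non-adherence {20c}:** "To handle the missing data multiple imputation will be used or complete case analysis will be used". The next sentence reads "The primary analysis will use the intention-to-treat principle".
- **Retention and follow-up {18b}:** for a participant lost to follow-up, "the data that will be collected till the time of loss to follow-up will be assessed and used in the analysis". The same section plans telephone follow-up after discharge.
- **Discontinuing allocated interventions {11b}:** the C-IVIG infusion is stopped for a serious adverse event, or "discontinued on patient request and the patient will be excluded from the study".

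Sample size {14} sets the allowance for loss at 30 per cent ("superiority margin 0.15, and drop rate 30").

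**The concern.** These rules do not select the same patients. One counts everyone randomised, one counts only those who finish, one leaves the choice between imputing and dropping open, one keeps partial follow-up, and one removes patients after randomisation. Nothing says which governs the primary endpoint or which is a sensitivity analysis, so the choice could be made with results in view.

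Two of the rules take randomised patients out of the comparison. Complete case drops anyone without full follow-up. The {11b} exclusion applies only where there is a C-IVIG infusion to stop, so it can remove patients from one arm only, and it does so because of an event after randomisation. If those who leave differ in prognosis between arms, the mortality contrast partly reflects who left.

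Informative loss is plausible here. Section {17b} foresees patients leaving against medical advice, {18b} foresees withdrawal for adverse events, and only participants are blinded ({17a}). There is also a gap of definition: the text does not say whether a patient who dies before day 28 has completed the study period, although death is the endpoint.

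**Working it through.** **1. The rules side by side**

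| Section | Who is counted | Consistent with intention-to-treat? |
|---|---|---|
| {20a}, first half of sentence; {20c}, last sentence | All randomised | Yes |
| {20a}, second half of sentence | Completers | No |
| {20c}, first sentence | Imputed, or complete case | Only if imputed |
| {18b} | All, with data up to loss | Yes, as censoring in Kaplan–Meier |
| {11b} | Excludes patients whose C-IVIG infusion is stopped | No, and one arm only |

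**2. How the 30% enters the plan's own figure**

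Inputs from {14}: survival 75% v 40%, margin 0.15, power 90%, ratio 2:1, drop rate 30%.

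Controls before loss = (0.40×0.60 + 0.75×0.25/2) × (z₁₋α + z₀.₉₀)² / (0.75 − 0.40 − 0.15)².

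At one-sided α = 0.05 this is 0.33375 × 2.926² / 0.04 = 71.5, so 72 controls and 216 in total. Then 72/0.70 = 102.9, so 103 controls and 309 in total, as stated. The 30% is therefore an inflation factor, N/(1 − 0.30). (The match is at one-sided 5%, not at the 99% confidence level that {14} states; that is a separate matter.)

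**3. Patients left out under complete case at 30% loss**

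206 × 0.70 ≈ 144 and 103 × 0.70 ≈ 72, so about 216 are analysed. About 62 + 31 = 93 randomised patients are not.

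**4. Extreme bounds**

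Suppose completers show the design rates and 30% of each arm has unknown status.

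- C-IVIG survival: 0.70×0.75 = 52.5% to 52.5% + 30% = 82.5%.
- Control survival: 0.70×0.40 = 28% to 28% + 30% = 58%.
- Difference: 52.5 − 58 = −5.5 to 82.5 − 28 = +54.5 points.

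**5. Illustration: no true effect**

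This compares completer proportions. True mortality is 40% in both arms, loss L is the same in both, and mortality among those lost (m) is an assumption, not a figure from the protocol. Completer mortality = (0.40 − L×m)/(1 − L).

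| L | m, C-IVIG v control | Completer mortality | Spurious benefit | Chance of significance in favour (nominal 2.5%) |
|---|---|---|---|---|
| 30% | 60% v 40% | 31.4% v 40.0% | 8.6 points | about 23% |
| 30% | 50% v 40% | 35.7% v 40.0% | 4.3 points | about 9% |
| 10% | 60% v 40% | 37.8% v 40.0% | 2.2 points | about 5.5% |
| 30% | 60% v 60% | 31.4% v 31.4% | 0 | 2.5% |

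For the first row at 144 v 72: standard error = √(0.314×0.686/144 + 0.40×0.60/72) = 0.070, z = 0.0857/0.0695 = 1.23, and Φ(1.23 − 1.96) ≈ 0.23.

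**The case against.** The strongest defence is that a coherent plan can be read out of the text. {20a} names Kaplan–Meier with the Breslow test as primary, {20c} says the primary analysis is intention-to-treat, and {18b} keeps data up to loss. Together these suggest all randomised patients, with losses censored, and completers as a second set. A reader might infer that the primary analysis is simply defined as complete case; the documents do not support that. But they do not establish the benign reading either: {20a} does not rank its two sets, {20c} still permits complete case, and {11b} still removes patients.

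A reader might also infer that the protocol expects 30% of vital status to be missing for arm-related reasons. It does not say so. The figure is a sample-size allowance. {17b} mentions leaving against advice only as a ground for unblinding and gives no rate. {18b} plans retention staff, calls after discharge and continued monitoring of patients who withdraw for adverse events, though not explicitly to day 28. Blinding of participants should also limit arm-driven departure.

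Finally, the 8.6 points and 23% belong to a comparison of completer proportions, not to the Breslow test, where lost patients contribute time until censoring. Informative censoring can bias that test too, but these figures do not measure it. The sign reversal in the bounds needs nearly every lost C-IVIG patient to die and nearly every lost control to survive. All of this stands and limits the size of the claim. It does not remove the contradiction.

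**Conclusion.** The point holds as an unresolved contradiction over the sole primary endpoint. It does not rest on detail that an analysis plan would normally supply: the article states the rules, and they conflict. Complete case and the {11b} exclusion each break intention-to-treat, and the open choice in {20c} allows the method to be settled after the data are seen.

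The number left out, about 93 of 309, follows from the 30% allowance. The bounds of −5.5 to +54.5 points add only the design survival rates for completers, and they are extremes. The bias figures (0 to 8.6 points over the scenarios shown) also depend on assumed mortality among those lost, and are illustrative only. If loss proves small, or mortality among the lost is alike in both arms, the bias is small or absent. The rules should be reconciled before any comparison by arm, which includes the interim looks.

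**What to change.** - **Analysis set.** State that the primary set is all randomised patients, as randomised. Delete the completers-only clause in {20a} as an analysis rule and the complete-case alternative in {20c}.
- **Discontinuation.** Reconcile {11b} with intention-to-treat: patients whose infusion is stopped stay in follow-up and in the analysis unless they withdraw consent. This concerns who is counted, not when the infusion should be stopped.
- **Vital status.** Obtain day-28 status for everyone, including patients discharged or who left against advice, through the telephone follow-up already planned in {18b}.
- **Kaplan–Meier/Breslow.** Censor only patients whose day-28 status remains unknown, at last contact. State that a death before day 28 is an event, not a failure to complete.
- **Day-28 proportion and relative risk.** Name one missing-data method in advance, for example multiple imputation using arm, site and last clinical status.
- **Sensitivity.** Keep complete case here, and add a best/worst-case or tipping-point analysis, because imputation corrects informative loss only as far as the variables used explain it.

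The sample size stays at 309. The cost is wording, plus a little more follow-up and analysis work.

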## Methods: participants, interventions, and outcomes

### Study setting {9}

The trial will be conducted in Karachi, Pakistan at Dow University of Health Sciences (Ojha Campus) and Sindh Infectious Disease Hospital and Research Center (SIDH).

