### Assignment of interventions: allocation

#### Sequence generation {16a}

Randomization will be stratified by site and will be in permuted blocks and the randomized sequence allocation will only be accessible to the site investigator. The randomization schedule will be generated by an independent statistician.

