### Data collection and management

#### Plans for assessment and collection of outcomes {18a}

Outcome, baseline, and other trial data will be collected by the study investigators. The clinical research associate will check the data. Nasopharyngeal/oropharyngeal swabs and blood samples will be sent to DUHS laboratory, where tests will be performed according to laboratory standard operating procedures (SOPs). Data reports can be found on HMIS (Hospital Management information system) and will be collected on clinical research forms (CRF).

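### Randomisation is stratified by site and baseline values are collected, but no named test uses site or adjusts for baseline: an avoidable, probably small loss of efficiency

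*Protocol article*

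**What the plan says.** All references are to the protocol article.

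- **Sequence generation {16a}:** "Randomization will be stratified by site and will be in permuted blocks". Study setting {9} and Recruitment {15} name two hospitals, both in Karachi.
- **Plans for assessment and collection of outcomes {18a}:** "Outcome, baseline, and other trial data will be collected by the study investigators".
- **Outcomes {12}:** several secondary outcomes are defined as changes: PaO2/FiO2 during the hospital stay and, over 5 days, "Change in C-reactive protein (CRP) levels, radiological findings, IL-6 level, and anti-SARS-CoV-2 antibody levels".
- **Statistical methods for primary and secondary outcomes {20a}:** the primary analysis is a Kaplan-Meier curve with a Breslow test "that compares the time to reach the primary end point in the trial groups". For the other outcomes, "Hypothesis testing of outcomes for the assessment of safety and efficacy parameters will be conducted by Mann-Whitney" U or an independent t-test, with a Shapiro-Wilk check of normality deciding between parametric and non-parametric tests. For proportions, "Categorical data will be compared with chi-square test, and value of the two-sided Fisher exact test will be recorded". Finally, "An estimate of the relative risk and 95% confidence interval will also be reported". The significance level is 0.05.

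No section names a stratified test, a regression model or a covariate adjustment.

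**The concern.** Permuted blocks within site keep the arms close to 2:1 in each hospital, so differences between hospitals largely drop out of the treatment comparison. A test that ignores site still counts that between-site variation in its standard error. If outcome differs between the hospitals, the standard error is too large, the true type I error falls below the nominal level and power is lost.

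The second issue is separate. A change score uses the baseline value by subtracting it in full. ANCOVA instead estimates how much of the baseline to remove, and it is usually more precise on the same data. Here the loss is in precision; the type I error is not affected.

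Third, the Shapiro-Wilk step lets the trial data choose the test, and with it the quantity compared (means or ranks), so neither is fixed in advance.

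At stake are somewhat wide intervals and some lost power, using data the trial already records.

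**Working it through.** **Inputs from the article.** N = 309 (206 + 103), 2:1 allocation, two sites, significance level 0.05, planned survival 75% v 40%, drop-out 30%, superiority margin 0.15.

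**Inputs not in the article (assumed).** Share of patients per site (taken as equal), outcome rates by site, correlation r between baseline and follow-up, and the two SDs.

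**The plan's own figure.** With unpooled variance and one-sided alpha 0.05:

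controls = (1.645 + 1.282)² × (0.40 × 0.60 + 0.75 × 0.25 / 2) / (0.35 − 0.15)² = 71.5, rounded up to 72.

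72 / 0.70 = 102.9, rounded up to 103 controls, hence 206 + 103 = 309. (The 99% level stated in Sample size {14} does not give 309; that is a separate matter.) Nothing below changes N.

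**Step 1: size of an unstratified test of mortality.** With balance within site and no treatment effect, the true variance of the contrast is to the assumed variance as W is to T. W is the mean of p(1 − p) over the sites, and T is p̄(1 − p̄) with p̄ the overall rate. True type I error = 2 × [1 − Φ(1.96 / √(W/T))].

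| Mortality by site | W | T | W/T | Type I error |
|---|---|---|---|---|
| 30% v 30% | 0.210 | 0.210 | 1.000 | 5.0% |
| 20% v 40% | 0.200 | 0.210 | 0.952 | 4.5% |
| 10% v 50% | 0.170 | 0.210 | 0.810 | 2.9% |

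Simulation with 103 v 52 patients per site (pooled z-test v Cochran-Mantel-Haenszel) agrees: 4.4–4.5% v 4.9–5.0% for 20% v 40%, and 2.9% v 5.0% for 10% v 50%. With equal sites both tests give 5.0%, so stratifying then costs nothing measurable.

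**Step 2: power.** Simulation of 309 patients with blocks of 6 within site and an odds ratio of 2 for survival, by control survival at the two sites:

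| Control survival | Unstratified | Stratified |
|---|---|---|
| 40% / 40% | 81% | 81% |
| 35% / 45% | 81% | 81% |
| 30% / 50% | 79% | 79% |
| 20% / 60% | 68% | 74% |
| 10% / 70% | 38% | 59% |

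The power loss is material only at gaps of 40 points or more.

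**Step 3: power at the planned effect.** For survival of 75% v 40%, tested against no difference:

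- 206 v 103: SE = √(0.1875/206 + 0.24/103) = 0.057, z = 0.35/0.057 = 6.1.
- 144 v 72 after 30% drop-out: SE = 0.068, z = 5.1.

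Power exceeds 99% in both cases, so stratification gains practically nothing if the planned effect is true.

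**Step 4: continuous change outcomes.** Let k = baseline SD / follow-up SD. In units of the follow-up variance, the change score has variance 1 + k² − 2rk and ANCOVA has 1 − r². The difference is (k − r)², which is never negative, so in large samples ANCOVA is never less precise. Ratio of ANCOVA to change-score variance:

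- k = 1: (1 + r)/2, that is 0.65, 0.75 and 0.85 at r = 0.3, 0.5 and 0.7 (35%, 25% and 15% less variance).
- k = 0.5, r = 0.5: 0.75/0.75 = 1.00, no gain.
- k = 2, r = 0.5: 0.75/3.00 = 0.25, a large gain.

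**The case against.** The strongest reply has four parts.

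**Site may not matter.** Two hospitals in one city recruit from one severity band, 5–15 L of oxygen. The article gives no site-level outcomes, so a large gap is not implied, and at the planned effect the power is above 99% anyway. This stands. A reader might infer from the stratified randomisation that the tests are definitely conservative; the article does not support that.

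**Change scores do use baseline.** This also stands. It would be wrong to say the change outcomes ignore baseline; the valid point is that subtraction is generally less efficient than adjustment. Nor can a gain of 15–35% be claimed for every change outcome, because it needs equal SDs. Those are least plausible for antibody levels, since the intervention infuses antibodies, and no scale is given for the radiological findings.

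**Strata and covariates are often left to an analysis plan.** Section {20a} never says that the analyses will be unadjusted, and a plan not shown may add adjustment. This lowers the weight of the point without removing it: the section names the primary test, the test for each data type, the effect measure and the significance level, and each is an ordinary two-group method as written.

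**Changing the analysis has costs.** Replacing the time-to-event primary comparison with a binary Mantel-Haenszel analysis would need a known 28-day status for everyone, whereas Section {18b} uses data up to loss to follow-up and 30% drop-out is allowed for. That objection is sound. The remedy should therefore add site to the existing primary test and leave that test in place.

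**Conclusion.** The point holds as a minor, nearly free improvement. The named tests do not use the factor that the randomisation used, and the change outcomes are not adjusted for baseline. The tests remain valid: there is no bias and no inflation of the type I error.

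The mortality comparison is conservative only as far as site is prognostic. With two equal sites (assumed), the effect on size is nil without a gap, about half a percentage point at a 20-point gap and about two points at a 40-point gap. For the continuous outcomes the gain from ANCOVA depends on r and on the ratio of the SDs; it is 15–35% of the variance for r between 0.3 and 0.7 with equal SDs, and can be nil or larger otherwise. The article fixes none of these quantities, so the actual size is unknown. The data-driven choice of test is plain in the text, but no figure is attached to it here.

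**What to change.** 1. **Primary outcome:** keep the Kaplan-Meier and Breslow comparison of 28-day mortality, stratified by site.
2. **Relative risk and categorical outcomes:** report a Mantel-Haenszel relative risk with its 95% confidence interval and Cochran-Mantel-Haenszel tests, both stratified by site.
3. **PaO2/FiO2, CRP, IL-6 and antibody levels:** analyse the follow-up value by ANCOVA on arm, site and baseline value. Name in advance the skewed markers to be log-transformed, and drop Shapiro-Wilk as the selector of the test.
4. **Deaths before measurement:** state how patients who die before the follow-up value is taken are handled. ANCOVA does not solve this, and neither does a change score.

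Cost: a few sentences of analysis wording and slightly more analysis work. Site and baseline are already recorded, N stays 309, and no extra patients, visits or data are needed. If a separate analysis plan already specifies this, the article should be brought into line with it.

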#### Interim analyses {21b}

An interim analysis will be performed after recruitment of 15%, 30%, and 60% participants in the trial. It will assess primary outcomes of the study particularly focusing on the safety and efficacy of the infused drug. Safety of the intervention will be monitored in terms of any immediate or serious adverse event that can be observed after the administration of the drug. The efficacy of the intervention will be noted in terms of the patient's improvement in clinical status as compared to the control group.

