## Discussion

This phase II/III clinical trial is an adaptive, randomized controlled, multi-center, single-blinded superiority trial of SARS-CoV-2 specific polyclonal IVIG (C-IVIG) versus standard of care for patients hospitalized with severe COVID-19. Single dose of C-IVIG in combination with the standard of care was found to be both safe and efficacious in our previous clinical trial phase I/II while increasing the survival rate and reducing the risk of disease progression [13]. There were no significant changes observed when different doses of C-IVIG were compared in the phase I/II; however, it was found that C-IVIG dosage of 0.15 g/kg have significantly improved the therapeutic response in severe COVID-19 patients. These results warrant the phase II/III clinical trial study of C-IVIG, in order to evaluate its safety and efficacy in large sample size by comparing outcomes (28-mortality, hospital stay and drug-related adverse events) of C-IVIG along with SOC in intervention group and SOC only in comparator group provided during the hospital stay.

Study participant selection for this study is based on the results of our previous clinical trial where severe patients had 100% survivability and early hospital discharge than critical patients and comparator group. We evaluated that hospital stay, reliance on mechanical ventilation, and burden on hospital could be reduced if C-IVIG is administered to the severe COVID-19 patients by delaying the disease progression.

This is an adaptive clinical trial to investigate the risk-benefit analysis of C-IVIG administration for severe COVID-19 at first and second interim of the study. Major outcome variables to be assessed for interim analysis are adverse events, 28-day mortality, and change in clinical status of the patients. Fate of this clinical trial is based on whether the C-IVIG is safe and efficacious. If the treatment modality is found to be safe but not efficacious as compare to comparator group, we might select different dosage of C-IVIG for further study participants; if interim analysis indicate association of serious adverse events with administration of C-IVIG or with significant high mortality ratio in intervention group than comparator group or if incidence rate of COVID-19 is low till the study completion date, then this clinical trial would be early terminated due to aforementioned reasons.

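### Two test rules compete for the 7-category clinical status scale, and the one that fits it by data type (chi-square/Fisher) ignores the order of the categories

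*Protocol article*

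**What the plan says.** Outcomes {12} lists as a secondary outcome "Clinical status according to 7 category ordinal Scale", running from not hospitalized without limitations (1) to death (7).

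Statistical methods {20a} covers primary and secondary outcomes and gives these rules, in this order:

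- For the choice between parametric and non-parametric tests: "Normality of continuous data will be checked by the Shapiro-Wilk test, and parametric or non-parametric tests will be applied accordingly".
- A rule by purpose, which also allows a t-test: "Hypothesis testing of outcomes for the assessment of safety and efficacy parameters will be conducted by Mann-Whitney".
- A rule by data type: "Categorical data will be compared with chi-square test, and value of the two-sided Fisher exact test will be recorded". A relative risk with 95% CI follows.
- A test level for all of them: "Hypothesis testing will be conducted at a significance level of 0.05".

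No rule mentions ordinal data or names the scale.

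Interim analyses {21b} sets three looks: "An interim analysis will be performed after recruitment of 15%, 30%, and 60% participants in the trial". On efficacy it says: "The efficacy of the intervention will be noted in terms of the patient's improvement in clinical status as compared to the control group". The same section also says the looks assess the primary outcomes. The Discussion gives a wider list: "Major outcome variables to be assessed for interim analysis are adverse events, 28-day mortality, and change in clinical status of the patients".

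**The concern.** An analyst who follows {20a} has two rules to choose from for this scale. The categorical rule fits its label; the efficacy-parameter rule fits its purpose. The choice matters because the tests answer different questions.

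A chi-square or Fisher test on a 7 x 2 table asks whether the two distributions differ in any way. A move from oxygen to home counts the same as a move from oxygen to ventilation. This has three consequences:

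- A consistent improvement is missed more often.
- A significant result need not mean improvement.
- No effect estimate on the scale follows. The relative risk that {20a} reports would need the scale to be cut at some point, and no cut is given.

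This reaches the interim looks because {21b} expresses efficacy as improvement in clinical status against control. Trial design {8} and section {11b} allow the regimen to change if the drug is not found efficacious.

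**Working it through.** **Which rule applies.** Read literally, the efficacy-parameter sentence would also send 28-day mortality and adverse events to a t-test or Mann-Whitney test. Outcomes {12} describes mortality as assessing safety and efficacy, yet it is a yes/no or time-to-event outcome. The sentence therefore cannot be fully literal. The workable reading sorts by data type: continuous data to t-test or Mann-Whitney after the normality check, categorical data to chi-square/Fisher. A scale labelled as having 7 categories then goes to chi-square/Fisher, with (7 - 1) x (2 - 1) = 6 degrees of freedom.

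**Inputs from the protocol.**

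- 206 v 103 patients, 2:1 allocation, 30% dropout, test level 0.05.
- Planned survival 75% v 40%, so deaths 25% v 60%. As an odds ratio for survival this is (0.75/0.25)/(0.40/0.60) = 3/0.667 = 4.5.
- Looks at 15%, 30% and 60% of 309, that is about 46, 93 and 185 patients, taken as 31 v 15, 62 v 31 and 124 v 62.
- After 30% dropout: 206 x 0.7 = 144 and 103 x 0.7 = 72.

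The protocol states no power for the scale, so there is no figure of its own to reproduce.

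**Assumptions.** The protocol gives no category split, so control-arm splits (category 1 to 7) were assumed:

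- A: .12, .12, .04, .05, .03, .04, .60
- B: .05, .15, .08, .06, .03, .03, .60
- C: .08, .10, .07, .06, .04, .05, .60
- D: .25, .25, .06, .06, .04, .04, .30
- E: .12, .18, .12, .15, .10, .08, .25

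The treated arm follows from a common odds ratio (OR): at each cut-point, the treated odds of being at or below that category equal OR times the control odds. With OR 4.5 and 60% control deaths this returns the planned 25% deaths.

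**Method.** Simulation with 2,000 to 3,000 runs per setting, two-sided 0.05, comparing Pearson chi-square on the non-empty categories with tie-corrected Mann-Whitney. Every recruited patient is assumed to have a category.

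**Power.**

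| Setting | Split | n | Chi-square | Mann-Whitney |
|---|---|---|---|---|
| OR 2, final | A | 206 v 103 | 0.59 | 0.85 |
| OR 2, final | B | 206 v 103 | 0.57 | 0.86 |
| OR 2, final | C | 206 v 103 | 0.55 | 0.87 |
| OR 2, final | D | 206 v 103 | 0.67 | 0.89 |
| OR 2, final | E | 206 v 103 | 0.69 | 0.91 |
| OR 2, after dropout | A | 144 v 72 | 0.39 | 0.72 |
| OR 2, 15% look | C | 31 v 15 | 0.05 | 0.20 |
| OR 2, 30% look | C | 62 v 31 | 0.15 | 0.40 |
| OR 2, 60% look | C | 124 v 62 | 0.34 | 0.66 |
| OR 4.5, 15% look | A | 31 v 15 | 0.43 | 0.73 |
| OR 4.5, 30% look | A | 62 v 31 | 0.79 | 0.96 |
| OR 4.5, 60% look | A | 124 v 62 | 0.99 | 1.00 |
| OR 4.5, final | A | 206 v 103 | 1.00 | 1.00 |

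At OR 2 and full size the loss runs from 0.91 - 0.69 = 22 points to 0.87 - 0.55 = 32 points. With no effect (OR 1), Mann-Whitney rejected in 4% to 6% of runs and chi-square in 3% to 5%, so the gain is not bought with false positives.

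**Direction.** Take control .05, .10, .20, .30, .20, .10, .05 and treated .18, .10, .12, .20, .12, .10, .18. Both are symmetric about category 4, so they differ in spread with no net shift. At 206 v 103, chi-square was significant in 99.5% of runs and Mann-Whitney in 3%.

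**The case against.** The strongest reply is that {20a} does not say chi-square is used for this scale. The sentence just before the chi-square rule assigns efficacy parameters to Mann-Whitney or a t-test, and {21b} treats clinical status as efficacy. Mann-Whitney respects order, so on that reading neither the loss of power nor the loss of direction arises. The relative risk named straight after the chi-square rule also suggests that binary items were in mind there. This stands to the extent that the protocol cannot be said to prescribe the wrong test. It does not settle the matter, because the efficacy sentence cannot be applied literally and the normality check is tied to continuous data.

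A reader might also infer that {20a} exposes the scale to a t-test on category numbers. That has little force. In simulations of splits A and D, Shapiro-Wilk rejected normality in at least one arm in every run, which leads to Mann-Whitney. A t-test would in any case keep order and direction, and where compared its power was within about one point of Mann-Whitney's.

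It can also be said that an article need not assign a test to each outcome. That is fair for an omission. Here, however, the article does state rules for secondary outcomes, and the two conflict over this one.

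Finally, the data were generated under proportional odds, which favours order-respecting tests, and the looks are triggered by recruitment, when some patients will not yet have a final category. Both points limit the sizes, not the direction under a consistent shift.

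**Conclusion.** The point holds as a conflict between two stated rules, in which the rule that fits the scale by data type gives the worse test. If chi-square/Fisher is used, power at an assumed common odds ratio of 2 and full size falls by about 22 to 32 points, and a significant result need not mean improvement. Under the full planned effect the loss is about 30 points at the 15% look and 17 at the 30% look, and is negligible from the 60% look on. All sizes rest on assumed category splits and a constant shift; only the direction of the loss under such a shift is firm.

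Two stronger readings are not supported. The first is that the plan definitely sends the scale to chi-square; the efficacy-parameter sentence leaves Mann-Whitney open. The second is that clinical status alone drives the interim decision. Section {21b} also refers to the primary outcomes, the Discussion adds adverse events and 28-day mortality, and nowhere is a decision tied to a p-value from this scale. The interim powers therefore describe a comparison at 0.05, not a stated decision rule. The scale is secondary, and the primary mortality analysis is unaffected.

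**What to change.** Add to {20a}: the 7-category clinical status (death = 7) is compared between arms with an order-respecting analysis, either the Mann-Whitney test or a proportional-odds model reporting a common odds ratio with 95% CI. The same analysis is used at the final analysis and whenever clinical status is compared at an interim look. Chi-square and Fisher tests are kept for binary and unordered variables.

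Either choice removes the conflict; the proportional-odds model also supplies an effect estimate. The cost is a sentence or two of wording and no new data, and the SPSS software already named runs both. The small downside is that a common odds ratio assumes a roughly constant shift across cut-points, so the percentage in each category should still be tabulated by arm.
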